## Abstract

**Background:**

The prevalence of alcohol consumption in Poland is estimated to be as high as 80% of the adult population. The use of stimulants is the second most common reason for seeking addiction treatment. However, treatment outcomes remain unsatisfactory, as 40–85% of individuals who complete various treatment programs relapse and fall back into addiction within 2 years following program completion.

**Methods:**

The 13-armed randomized controlled trial aimed to assess the effectiveness of a mobile app-based self-guided psychological intervention delivered *via* a smartphone app (*Nałogometr*) in reducing craving and lapse risk in problematic alcohol or stimulants use. Participant recruitment and data collection will be performed from June 2022 to September 2022. The 4-week mobile intervention program will include short-term and long-term intervention modules based mainly on mindfulness and cognitive-behavioral therapy. Intervention effectiveness assessment will include Ecological Momentary Assessment. That is, we will collect longitudinal data on a set of characteristics of day-to-day functioning. The primary outcomes will include a self-reported number of lapses and addiction craving level. In contrast, the secondary outcomes will be the severity of problematic substance use, anxiety and depression scores, and life satisfaction scores.

**Conclusion:**

This study will establish how mobile app-based self-guided psychological interventions can help reduce craving and lapse risk in alcohol and stimulant dependence. If successful, this randomized controlled trial (RCT) may provide an innovative, easily available, and cost-effective mHealth approach for craving and lapse risk in substance addictions.

**Clinical trial registration:**

[https://clinicaltrials.gov/], identifier [NCT054 34429].

## 1 Introduction

Addiction is a highly prevalent and chronic disorder, harming individuals and society by placing a significant burden on social policy and medical resources. A major issue in addiction is its relapsing nature, with the propensity to relapse long after the more obvious signs of acute withdrawal have abated (1). Alcohol and stimulants (including amphetamines, methamphetamine, or methcathinone) dependencies manifest by an impaired ability to control use, increasing priority over other activities, and persistence of use despite harm or negative consequences, often accompanied by a craving to use substance (2). The physiological symptoms of addiction include tolerance, withdrawal symptoms, or repeated use of substances to prevent withdrawal symptoms. Addiction is usually diagnosed if alcohol or substance use occurs continuously for at least 3 months or if dependence symptoms occur for at least 12 months.

Globally, in the adult population (aged ≥ 15 years), a person consumes 6.43 liters of pure alcohol per year (3). Approximately 18.4% of the adult population reported heavy episodic drinking (≥ 60 g of alcohol on one occasion) in the past 30 days. Central, Eastern, and Western Europe reported higher alcohol consumption and a higher percentage of heavy consumption among users (49.5, 46.9, and 40.2%, respectively) than North Africa and the Middle East. Central sub-Saharan Africa showed the highest proportion of heavy consumption (78.9%) with a relatively low per capita consumption (3). Alcohol addiction was the most prevalent substance of dependence, with 63.5 million cases in 2015. The highest age-standardized rate of alcohol dependence was in Eastern Europe (2,786.7 per 100,000 people) and the lowest in North Africa and the Middle East (274.2 per 100,000 people). In 2018, the rate of alcohol use in Poland was 79.9%, while the percentage of drug use was 5.4% (population aged 15–64). The highest prevalence of drug use was registered in Spain (11.9% in 2017), Netherlands (11.8% in 2018), and France (11.4% in 2017). The lowest prevalence of alcohol use was in Cyprus (2.2% in 2016) and Hungary (2.3% in 2015).

The global prevalence of amphetamines and cocaine use is about 0.77 and 0.35%, respectively (4). In 2015, amphetamine and cocaine dependence was estimated to be 6.6 million and 3.9 million cases. The region of North America had one of the most prevalent rates of cocaine dependence, 301.2 per 100,000 people. Australia and New Zealand had the highest prevalence of age-standardized rates of amphetamine dependence (491.5 per 100,000 people) and high rates of cocaine use dependence (160.6 per 100,000 people). Age-standardized amphetamine and cocaine dependence prevalence were lowest in central sub-Saharan Africa and eastern and western sub-Saharan Africa. In the population aged 15–34, the prevalence of drug use in the last year was higher than in the entire population (aged 15–64). The highest rates were in France (22.6% in 2017), Netherlands (21.5% in 2018), and Italy (21.3% in 2017), and the lowest in Hungary (3.5% in 2015), Cyprus (4.3% in 2016) and Greece (4.5% in 2015) (5). In Poland, the proportion of drug users aged 15–34 was 10.4% (2018). Among the general population, 4% of respondents (15–34 years old) admitted to using amphetamines or cocaine (0.5%) in the last year, with a higher rate among men than women. Amphetamines are the second drug (after cannabis), because of which people started treatment in Poland (27%), followed by methamphetamine (9%) and cocaine (2.2%) (6).

Maintaining abstinence is one of the primary goals of addiction treatment. However, treatment outcomes remain unsatisfactory, primarily due to the high rate of relapses. It is estimated that 40–80% of individuals who successfully complete various treatment programs relapse and fall back into addiction (7, 8). Among different approaches, cognitive-behavioral therapy (CBT) and cue-exposure therapy (CET) have proven to be effective in treating substance additions (9). CBT can help cope with mood disturbances and addiction cravings by restructuralization of maladaptive beliefs and behaviors related to addiction and can also be effective in treating substance use disorders in clinical settings in combination with pharmacotherapy (10). The additional option is a computer-assisted CBT, as computers and mobile devices with Internet access are now readily available. A six-module computer-assisted CBT program effectively adjuncts to standard substance use disorder therapy (11). The most significant advantage of such a solution is that it is much cheaper than standard CBT and does not require constant access to clinicians.

Mindfulness integrates well with dialectical behavior therapy (DBT) and acceptance and commitment therapy (ACT) which can be adapted for treating substance and behavioral addictions (12, 13). These approaches in psychotherapy focus on acceptance, cognitive defusion, and flexible attention to the present (14). Standardized mindfulness techniques effectively reduce emotional distress and alleviate symptoms of psychiatric disorders (15). Mindfulness-Based Interventions (MBIs) are used in treating substance use disorders (nicotine, alcohol, cocaine, and opioids) as they address the mechanisms of addiction. MBIs programs usually last 8 weeks and target mindfulness skills to deal with addiction in different situations of everyday life, e.g., by being mindful of one’s craving (16). Mindfulness techniques such as focused attention or open monitoring aim to train attentional reorienting skills, metacognition, reappraisal, and inhibitory control, which are essential in coping with addictive behaviors (17). Mindfulness meditation reduces psychological distress, decreases rumination (18), negative affect and state anxiety, and increases positive affect (19). MBIs were found effective regarding withdrawal symptoms, craving, and negative consequences of substance use (20). Although Mindfulness-based Relapse Prevention is gaining recognition as a therapeutic strategy, yielding minor effects on withdrawal or craving versus comparator interventions, further data are needed to confirm it as an effective strategy. CBT, MBIs, and treatment as usual (TAU) did not differ in substance use frequency and relapse. ACT effectively reduces substance use (21), and the effects of MBIs and ACT on alcohol dependence did not differ from other standardized treatment approaches.

Journaling is a common therapeutic tool used in two forms—expressive writing and gratitude journaling (22). The first journaling technique is based on writing about crucial thoughts and emotions for about 20 minutes in up to 4 sessions (23). Gratitude journaling is a diary that includes everything a patient is grateful for and aims to focus on the positive aspects of everyday life (24). The low risk of adverse effects, low resource requirement, and focus on self-efficacy make journaling a tool that can be easy to combine with other evidence-based forms of therapy (25). There needs to be evidence-based guidance about the utility of journaling as a non-pharmacological treatment. There are only limited efforts of a systematic review of the efficacy of journaling (25). We should note that there are studies indicating no benefits from journaling when using alcohol or illegal drugs (23), and there are concerns that journaling is associated with becoming a passive observer, too conscious, or overthinking. Self-monitoring involves being aware of emotions and behaviors in response to different situations, and it is the ability to regulate and modify behaviors in response to various factors. Internet-based self-monitoring interventions offer high usability, accessibility, interactive multimedia, graphical features, tracking systems, sensor-based devices, and individualized feedback (26). Digital diaries for treating bipolar disorder, pain, weight and sleep management, chemotherapy, and borderline personality disorder were promising and usable in digital self-monitoring (26). Mobile phone applications combined with new possibilities of self-monitoring increase data quality, enhance participants to registration, examine the risk and protective factors during therapy, and investigate the predictors of successful treatment.

Ecological Momentary Assessment (EMA) involves the repeated sampling of subjects’ current behaviors and experiences in real time in natural environments. EMA holds the unique promise to advance the science and practice of clinical psychology. Surveys were a traditional tool in research on addictions, but they are only point measurements that do not capture the dynamics of changes in behavior. EMA was used in tobacco and alcohol use disorders and relatively less often in heroin and cocaine research regarding both in-treatment and recovery patients (27). In methamphetamine- or cocaine-dependent participants, studies with EMA assessed stress and the cognitive, affective, and motivational factors on drug craving (28–30). EMA used in self-monitoring was effective and reliable in treating and assessing eating disorder urges (31). EMA and self-monitoring methods support behavior change and self-management by increasing the awareness of addictive behaviors and triggers, goal progress tracking, self-rewards, reminders, reinforcement, and personal feedback (32).

Due to the high risk of relapse in addiction (33), mobile health (mHealth) interventions could be a valuable tool for enhancing the post-therapeutic effects after treatment (34). The mHealth interventions delivered through smartphone apps are gaining popularity; however, the evidence for their effectiveness often remains unsolved (35). With over 300,0000 health applications available (36), a small number have been clinically tested before entering the market (37). Currently, there are no evidence-based mobile apps in Poland that effectively reduce craving and lapse risk in substance use disorders. The present study aims to test the effectiveness of mobile app-based self-guided psychological intervention delivered *via* a smartphone app (*Nałogometr*) involving EMA in reducing craving, lapse risk, and substance use (alcohol, stimulants).

## 2 Methods

### 2.1 Aim

The study aimed to evaluate the effectiveness of long-term and short-term intervention modules in reducing craving and lapse levels in alcohol and stimulant problematic use.

### 2.2 Participants

Recruitment takes place from June 2022 until September 2022 to ensure the targeted sample size is reached. Participants will be recruited *via* newsletters, advertisements, and social media. The study will be conducted using the proprietary mobile application *Nałogometr* to collect all relevant measurements. Inclusion criteria will include self-reported problematic alcohol or stimulant use, being 18 or over, speaking Polish fluently, using Android or iOS smartphones, and accepting informed consent. We recruit only people living in Poland.

### 2.3 Sample size calculation

To determine the sample size, a simulation-based power analysis was performed. For the simulation, we assumed a linear mixed-effects model (with random participant-level intercepts), 21 data points (EMA entries) per participant. Based on the results of previous substance use reduction mobile intervention studies [for a review, see Staiger et al. (38)], small effect size of the treatment, i.e., introducing an intervention, was also assumed in the simulation. This analysis suggested that a minimum sample size of 650 participants will be necessary to achieve 80% power of detecting a treatment effect. Due to the nature of the study, i.e., a nationwide study of problematic substance (alcohol and stimulants) use, our sampling strategy has been designed. to maximize the demographic diversity of the resulting sample, particularly with respect to demographic characteristics (e.g., gender, age, geographic and socioeconomic setting) within each addiction profile.

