### 2.6 Randomization

Randomization will be applied using an automated balancing algorithm. The algorithm will aim to partition participants into groups based on the initial onboarding assessment to make the resulting groups as balanced as possible concerning the characteristics outlined in the study design section, i.e., (1) primary addiction type; (2) participation in addiction-related therapy; (3) gender; (4) age; (5) addiction severity; (6) abstinence duration. Following randomization, participants in groups 1–12 will receive access to the intervention modules following a 5-day delay. In conditions 1:10, participants get access to the short-term intervention module and one type of long-term intervention. In condition 11, participants get access to the short-term intervention module and all long-term interventions. In condition 12, participants get access only to the short-term intervention module.

Participants in the waitlist control group will be able to access all intervention materials 5 weeks following study enrollment (see Figure 1).

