### 2.9 Data analysis

We will use factorial design mixed-effects models to compare questionnaire battery scores between experimental groups and the control across measurements. In addition, we will perform an interrupted time series analysis to compare the longitudinal effects of the introduction of different types of interventions on longitudinal EMA outcomes.

We will include participants who complete at least 21 EMA assessments spread across the intervention testing period of 5 weeks. Furthermore, for the 6-month follow-up intervention effects retention analysis, we will include participants who complete at least three EMA assessments within the follow-up period. Moreover, in each intervention group, we will retain participants who log onto the app and use the long-term and short-term self-guided intervention modules at least four times and once, respectively, defined as minimal therapeutic exposure. Finally, for the secondary outcome analysis, we will include participants who complete the baseline and at least one follow-up assessment.

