## 3 Discussion

This study protocol describes a randomized controlled trial designed to determine the effectiveness of self-guided psychological intervention modules delivered *via* a smartphone app (*Nałogometr*). We aim to examine whether and which interventions can effectively reduce craving and lapse risk in problematic alcohol or stimulant use. The embedded trial and analysis will evaluate the effectiveness of intervention modules for alcohol or/and stimulants use. In exploratory analyses, we investigate whether user engagement moderates or changes in psychological functioning measures (e.g., sensation seeking, impulsivity, stress coping, emotion regulation) mediate the effectiveness of the interventions. We hope to determine if these interventions delivered through mobile devices can be effective and contribute to future prevention or therapy addiction programs. The wide availability and accessibility of developed interventions are a substantial advantage. Mobile app interventions may reduce treatment barriers by staying anonymous and avoiding stigma and may be especially useful in places where professional help is unavailable (49–52). We plan a 6 months follow-up to conduct a longer-term evaluation and check the sustainability of the potential change in the user’s behavior–it is an essential factor for relapse prevention through the management of craving. Such a complex study of 13 conditions will allow us to understand better which long-term interventions are most effective. We include multiple intervention types to better assess their effectiveness across diverse individuals. One limitation of the present study could be that the participant dropout will be higher than expected based on previous research (53, 54). Due to the lack of personal contact with researchers and no additional incentives, e.g., prizes or monetary remuneration, the commitment to participate throughout the study may be lower, and motivation may decrease over time.

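### The 80% power at 650 participants is stated for one unnamed treatment effect and is unsupported for the 12 arm-versus-waitlist comparisons, two primary outcomes and restricted analysis set that the trial plans

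*Protocol article*

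**What the plan says.** Section 2.3 rests on a simulation in which "we assumed a linear mixed-effects model (with random participant-level intercepts), 21 data points (EMA entries) per participant". The effect is described only in words: "small effect size of the treatment, i.e., introducing an intervention, was also assumed in the simulation". The conclusion is "This analysis suggested that a minimum sample size of 650 participants will be necessary to achieve 80% power of detecting a treatment effect". No alpha, numeric effect, variance components, outcome or contrast is given.

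Other sections set the frame that this figure has to fit:

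- The Abstract describes "The 13-armed randomized controlled trial". Section 2.6 makes this 12 intervention conditions and one waitlist control, and gives no allocation ratio: "Randomization will be applied using an automated balancing algorithm".
- Section 2.8.1 names two primary outcomes, lapses and craving.
- Section 3 sets the aim of finding whether, and which, interventions work, and says that the 13 conditions will help to show which long-term modules are most effective.
- Section 2.9 restricts the analysis: "We will include participants who complete at least 21 EMA assessments spread across the intervention testing period of 5 weeks". In the intervention arms it also retains only those who reach a minimal exposure to the modules.
- Section 2.2 links the target sample size to the recruitment period. Section 3 names as a possible limitation that "the participant dropout will be higher than expected based on previous research".

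**The concern.** The power statement covers one treatment effect, while the stated question is about individual modules on two outcomes. With equal allocation, 650 over 13 arms is 50 per arm. The simulation describes people who have already met the entry threshold, whereas the target is tied to recruitment. The exclusions in section 2.9 therefore come off a number already called the minimum, unless 650 means analysed participants.

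At stake is how single-module results are read. A null result for a module would be taken as coming from a trial with 80% power, when the chance of detecting a small effect of that module may be much lower.

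**Working it through.** **Reproducing 650.** This is not possible. Alpha, the numeric effect, the ICC and the contrast are not stated, so 650 can be neither confirmed nor refuted. Two checks remain.

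**Check 1: free of ICC and effect size.** Suppose 650 is the minimum for 80% power on one two-sided 5% test. The noncentrality is then 1.960 + 0.842 = 2.802, and power at noncentrality λ and level α is Φ(λ − z(1−α/2)).

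*Loss of participants* (λ scales with the square root of the fraction analysed):
- 80% analysed: λ = 2.802 × √0.8 = 2.506; Φ(2.506 − 1.960) = 71%. Analysing 650 would need 650/0.8 = 813 recruited.
- 50% analysed: λ = 2.802 × √0.5 = 1.981; Φ(0.021) = 51%. Analysing 650 would need 1300 recruited.

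*Stricter level* (Bonferroni as an illustration; no rule is stated):
- alpha/2 (two outcomes): Φ(2.802 − 2.241) = 71%
- alpha/12 (twelve arms): Φ(2.802 − 2.865) = 47%
- alpha/24 (both): Φ(2.802 − 3.078) = 39%

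*Choice of contrast* (equal arms assumed). If 650 was sized for two groups of 325, a 50 v 50 comparison has λ = 2.802 × √(50/325) = 1.099 and 19.5% power. If it was sized for 600 pooled v 50 waitlist, λ = 2.802 × √[(1/600 + 1/50)/(2/50)] = 2.062 and power is 54%.

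**Check 2: one arm against waitlist.** Assumptions, not in the document: equal allocation (650/13 = 50 per arm), d = 0.2 in total-SD units, two-sided 5%, group-by-phase contrast, random intercept only, 21 entries each.

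SE = √{2(1 − ICC)(1/pre + 1/post)/50}; λ = 0.2/SE.

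Two splits of the 21 entries were used. A 5-day delay in a 5-week period implies 21 × 5/35 = 3 before access and 18 after. A 5/16 split is more favourable.

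Worked example (3/18, ICC 0.5): SE = √{2 × 0.5 × (1/3 + 1/18)/50} = 0.0882; λ = 2.268; power = Φ(0.308) = 62%.

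| Split, level | ICC 0.3 | ICC 0.5 | ICC 0.7 |
|---|---|---|---|
| 5/16, unadjusted | 65% | 79% | 95% |
| 3/18, unadjusted | 48% | 62% | 83% |
| 5/16, alpha/24 | 23% | 38% | 69% |
| 3/18, alpha/24 | 12% | 21% | 44% |

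**Varying response.** Random intercepts alone assume that everyone responds alike. Adding a between-person response SD of 0.3 (assumed) in the treated arm only, SE = √{[2(1 − ICC)(1/5 + 1/16) + 0.09]/50}. Unadjusted power with the 5/16 split falls from 65/79/95% to 55/66/81%. The pooled contrast (600 v 50, ICC 0.5) barely moves, from 96% to about 95%, because the waitlist arm limits its precision and has no treatment response to vary.

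**The case against.** The strongest reply is that nothing here is shown to be wrong. A reader might infer that 80% does not hold, or that 650 suits at most one unadjusted comparison with nobody excluded. The document does not support either reading:

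- With the 5/16 split and ICC 0.7, one arm against waitlist still has 85% power with only 35 of 50 analysable. With the 3/18 split and all 50, 80% is reached unadjusted from an ICC of about 0.67, and at alpha/24 from about 0.83.
- Twenty-one entries is a floor per person. Three prompts a day for 5 weeks is 3 × 35 = 105 entries; the two daily windows named in section 2.6 give 70. Some loss of entries is therefore already built in. With all 70 entries (10 before, 60 after), even 25 per arm would have 70/83/97% unadjusted power at ICC 0.3/0.5/0.7. Full completion is optimistic, but the table in the working is pessimistic on this point.
- Since 21 is also the inclusion threshold, 650 could mean analysed participants. The dropout remark in section 3 is conditional and does not prove that no allowance was made.
- The simulation inputs and any multiplicity rule may stand in the preregistration or an analysis plan, neither of which is shown.

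All of this limits the wording. What remains is that the article states a power figure, and the figure is not connected to the comparisons or analysis set described in the same article. A multiplicity rule kept elsewhere would lower the power for each test unless 650 already allows for it. The recruitment wording in section 2.2 points towards 650 recruited. Rescue by a very high ICC also relies on an identical response in everyone.

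**Conclusion.** The point stands as a gap between the stated power and the planned trial, not as a proven arithmetic error. The 80% refers to one unnamed effect. It is unsupported for single arms against waitlist, for two primary outcomes, and for the set left after the section 2.9 exclusions.

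The firmest result needs only the premise that 650 is the minimum for one two-sided 5% test: any exclusion or adjustment then takes power below 80%, to between 39% and 71% in the cases shown. The single-arm figures rest on more assumptions (equal arms, d = 0.2, 21 entries, the ICC range) and run from 48% to 95% unadjusted and from 12% to 69% at alpha/24. The width of these ranges is itself a reason to state the inputs.

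**What to change.** In section 2.3, state the contrast, outcome, alpha and effect size to which the 80% refers, and whether 650 is randomised or analysed.

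Rerun the simulation with 13 arms, the expected exclusions under section 2.9, the multiplicity rule, and a random treatment response in the treated arms only. Report the resulting power for single-arm contrasts and, separately, for pooled arms 1–12 against waitlist. Whether the pooled contrast should be tested first is a design choice for the investigators; this point does not depend on it.

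The cost is a rerun and a reworded section, with no extra enrolment. The downside is a visibly lower stated power per arm.
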